| Statistical Considerations:            | The analysis will be exploratory and primarily employ descriptive statistical methods. Inferential methods will be used to highlight interesting aspects of the data. Unless otherwise specified statistical tests will be two sided and conducted at the 5% significance level. Corresponding 95%-confidence intervals will be presented and no correction for multiplicity will be applied.                                                                                                                                                                                                                                                                                                                                                                                                                                                                                                                                                                                                                                                        |
| GCP Statement:                         | This trial will be conducted in compliance with the protocol, the current version of the Declaration of Helsinki, the ICH-GCP as well as all national legal and regulatory requirements.                                                                                                                                                                                                                                                                                                                                                                                                                                                                                                                                                                                                                                                                                                                                                                                                                                                             |

**ABBREVIATIONS**

|                    |                                                                             |
|--------------------|-----------------------------------------------------------------------------|
| AE          | Adverse Event                                                        |
| API         | Active Pharmaceutical Ingredient                                     |
| ASR         | Annual Safety Report                                                 |
| AUC         | Area Under the Concentration Time Curve                              |
| BASEC       | Business Administration System for Ethical Committees                |
| BD          | Biodistribution                                                      |
| BDI         | Beck's Depression Inventory                                          |
| b.i.d.      | Bis in die (twice a day)                                             |
| CA          | Competent Authority                                                  |
| CEC         | Competent Ethics Committee                                           |
| CI Bern     | Clinical Investigation Bern                                          |
| ClinO       | Ordinance on Clinical Trials in Human Research                       |
| eCRF        | Electronic Case Report Form                                          |
| DB          | Database                                                             |
| DSMB        | Data Safety Monitoring Board                                         |
| EDC         | Electronic Data Capture                                              |
| ESS         | Epworth Sleepiness Scale                                             |
| GBS         | Guillain-Barré Syndrome                                              |
| GCP         | Good Clinical Practice                                               |
| GM1         | Monosialotetrahexosylganglioside                                     |
| HRA         | Human Research Act                                                   |
| IB          | Investigator's Brochure                                              |
| IMC         | Internal Monitoring Committee                                        |
| IMP         | Investigational Medicinal Product                                    |
| i.m.        | Intramuscular (injection)                                            |
| ISF         | Investigator Site File                                               |
| i.v.        | Intravenous (injection)                                              |
| LEDD        | Levodopa Equivalent Daily Dose                                       |
| LCT         | Levodopa Challenge Test                                              |
| MDS - UPDRS | Movement Disorder Society's Unified Parkinson's Disease Rating Scale |
| MAD         | Multiple Administration Dose                                         |
| MSD         | Maximal Suitable Dose                                                |
| MoCA        | Montreal Cognitive Assessment                                        |
| NMSQuest    | Non-Motor Symptoms Questionnaire                                     |
| PDQ39       | Parkinson's Disease Questionnaire 39                                 |
| PI          | Principal Investigator                                               |
| PK          | Pharmacokinetics                                                     |
| SAD         | Single Ascending Dose                                                |
| SAE         | Serious Adverse Event                                                |
| SAS         | Starkstein Apathy Scale                                              |
| SMP         | Safety Management Plan                                               |
| SNCTP       | Swiss National Clinical Trials Portal                                |
| s.c.        | Subcutaneous (injection)                                             |
| SOP         | Standard Operating Procedure                                         |
| SUSAR       | Suspected Unexpected Serious Adverse Reaction                        |
| TLN         | Talineuren                                                           |
| TMF         | Trial Master File                                                    |
| UPN         | Unique Patient Number                                                |

## STUDY SCHEDULE

[illegible]

Table 1: Schedule for dose escalating part (part 1)

| Trial Periods                 | Screening | Baseline | Treatment (T) | PK 24h | PK 48h | PK 72h | PK 96h | T | T  | T  | T  | T  | T  | T  | Final assessment | Follow-up |
|-------------------------------|-----------|----------|---------------|--------|--------|--------|--------|---|----|----|----|----|----|----|------------------|-----------|
| Visit                         | 1         | 2        | 3             | 4      | 5      | 6      | 7      | 8 | 9  | 10 | 11 | 12 | 13 | 14 | 15               | 16        |
| Time (weeks)                  | -4 to -1  | 1        | 1             | 1      | 1      | 1      | 1      | 2 | 3  | 4  | 5  | 6  | 7  | 8  | +1               | +4        |
| Time (days)                   | -28 to -1 | 0        | 1             | 2      | 3      | 4      | 5      | 8 | 15 | 22 | 29 | 36 | 43 | 50 | +7               | +28       |
| Patient information & consent | x         |          |               |        |        |        |        |   |    |    |    |    |    |    |                  |           |
| In-/Exclusion Criteria        | x         |          |               |        |        |        |        |   |    |    |    |    |    |    |                  |           |
| Pregnancy Test                | x         |          |               |        |        |        |        |   |    |    |    |    |    |    |                  |           |
| Medical History               | x         |          |               |        |        |        |        |   |    |    |    |    |    |    |                  |           |
| Clinical Assessment           | x         |          |               |        |        |        |        |   |    |    |    |    |    |    | x                | x         |
| Vital Signs                   | x         | x        | x             |        |        |        |        | x | x  | x  | x  | x  | x  | x  | x                | x         |
| MoCA                          | x         |          |               |        |        |        |        |   |    |    |    |    |    |    | x                |           |
| Lab tests                     | x         | x        |               |        |        |        |        | x | x  | x  | x  | x  | x  | x  | x                | x         |
| Levodopa Challenge Test       |           | x        |               |        |        |        |        |   |    |    |    |    |    |    | x                |           |
| TLN Infusion                  |           |          | x             |        |        |        |        | x | x  | x  | x  | x  | x  | x  |                  |           |
| Blood collection (PK)         |           |          | x             | x      | x      | x      | x      |   |    |    |    |    |    |    |                  |           |
| MDS-UPDRS                     |           |          | x             |        |        |        |        | x | x  | x  | x  | x  | x  | x  | x                | x         |
| PDQ-39                        |           | x        |               |        |        |        |        |   |    |    |    |    |    |    | x                |           |
| ESS                           |           | x        |               |        |        |        |        |   |    |    |    |    |    |    | x                |           |
| BDI                           |           | x        |               |        |        |        |        |   |    |    |    |    |    |    | x                |           |
| SAS                           |           | x        |               |        |        |        |        |   |    |    |    |    |    |    | x                |           |
| NMSQuest                      |           | x        |               |        |        |        |        | x | x  | x  | x  | x  | x  | x  | x                |           |
| LEDD                          |           | x        |               |        |        |        |        | x | x  | x  | x  | x  | x  | x  | x                | x         |
| Adverse events recording      |           |          | x             | x      | x      | x      | x      | x | x  | x  | x  | x  | x  | x  | x                | x         |

Table 2: Schedule for dose consolidating part (part 2)

| Trial Periods                 | Re-consent | T | T | T  | T  | T  | T  | T  | T  | T  | Final assessment | Follow-up |
|-------------------------------|------------|---|---|----|----|----|----|----|----|----|------------------|-----------|
| Visit                         | 0          | 1 | 2 | 3  | 4  | 5  | 6  | 7  | 8  | 9  | 10               |           |
| Time (weeks)                  | -4 to -1   | 1 | 2 | 3  | 4  | 5  | 6  | 7  | 8  | +1 | +4               |           |
| Time (days)                   | -28 to 0   | 1 | 8 | 15 | 22 | 29 | 36 | 43 | 50 | +7 | +28              |           |
| Patient information & consent | x*         |   |   |    |    |    |    |    |    |    |                  |           |
| Clinical Assessment           |            |   |   |    |    |    |    |    |    | x  | x                |           |
| Vital Signs                   |            | x | x | x  | x  | x  | x  | x  | x  | x  | x                |           |
| MoCA                          |            |   |   |    |    |    |    |    |    | x  |                  |           |
| Lab tests                     |            | x | x | x  | x  | x  | x  | x  | x  | x  | x                |           |
| Levodopa Challenge Test       |            |   |   |    |    |    |    |    |    | x  |                  |           |
| TLN Infusion                  |            | x | x | x  | x  | x  | x  | x  | x  |    |                  |           |
| Blood collection (PK)         |            |   |   |    |    |    |    |    |    |    |                  |           |
| MDS-UPDRS                     |            | x | x | x  | x  | x  | x  | x  | x  | x  | x                |           |
| PDQ-39                        |            |   |   |    |    |    |    |    |    | x  |                  |           |
| ESS                           |            |   |   |    |    |    |    |    |    | x  |                  |           |
| BDI                           |            |   |   |    |    |    |    |    |    | x  |                  |           |
| SAS                           |            |   |   |    |    |    |    |    |    | x  |                  |           |
| NMSQuest                      |            | x | x | x  | x  | x  | x  | x  | x  | x  |                  |           |
| LEDD                          |            | x | x | x  | x  | x  | x  | x  | x  | x  | x                |           |
| Adverse events recording      |            | x | x | x  | x  | x  | x  | x  | x  | x  | x                |           |

Table 3: Schedule of assessment prolongation (optional)

## **1.6 Internal Monitoring Committee (IMC)**

The IMC is the executive board concerning decisions during the trial (e.g., dose escalation procedure) and consists of the PI, the manager medical affairs, and an external Medical Doctor as an independent medical monitor. The sponsor guarantees the independence of the later as he/she has an important role within the IMC. Every discussion/decision of the IMC will be documented and filed in the trial master file (TMF). Decisions to pursue the trial for each patient will be taken unanimously by the three members. This guarantees that the external member's opinion will have the same value as of the other members.

In principle, the IMC will meet on a weekly basis during the treatment phase in order to evaluate all safety data reported until that timepoint. All data will be verified and SAEs re-assessed before.

## **1.7 Data Safety Monitoring Board (DSMB)**

The Data Safety Monitoring Board (DSMB) is an advisory board, that is independent from the sponsor and which has no competing interests. Its main objective is to ensure the integrity and safety of participants of the NEON trial by providing unbiased review of raw (not aggregated) clinical trial data. The DSMB consists of 3 independent experts in the field. More details are provided in the trial specific DSMB charter, that serves as guideline of operating principles for DSMB members to oversee patient safety and data quality, to review trial efficacy and progress and to ensure the validity and integrity of the trial on a regular basis.

The DSMB will meet after dose level 5, 10 and 15 during part 1 of the trial, after the maximal suitable dose (MSD) has been defined and after last patient last visit.

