#### 6.1.1 Dose escalation (Part 1)

In this part a group of 3 patients will receive a single weekly dose that will be increased according to the schedule defined. In parallel, meaning that the first patient will receive a dose X on week Y, if the safety assessment is positive (see **Section 8.3 Dose modifications**) then the following week (Y+1) this patient will receive the next dose (X+1), on that week (Y+1) two other patients will receive the same dose X to confirm the safety assessment. *In fine*, every week patient 1 will receive one dose at the same time that patients 2 & 3 receive the preceding dose.

This weekly increase has been elected to allow rapid determination of the MSD and rapidly reach a dose level that will be beneficial for the patients involved in this trial. This is allowed by the fact that GM1 is expected to be safe and no clear AE are foreseen within this dose range. Furthermore, the 1 + 2 pattern allows one week observation of each dose increase in 1 patient before infusing 2 more.

The first dose level starts at 6 mg which will increase to 12 and 60 mg, then increasing by equal steps of 60 mg up to 720 mg. The escalation will be stopped individually according to the decision matrix detailed in the **Section 8.3 Doses modifications**. The three first steps of the dose are purposely low to account for any possible unexpected effects of the formulation.

Throughout the escalation part, all patients will be monitored twice weekly to record AEs and document them. Monitoring will take place once before each TLN infusion (beginning of the week) and a second time by the end of each week (performed by the principal investigator) to collect AE and allow enough time for the IMC to review them and take their decision on the next infusion/dose modification/delay.

At the end of the escalation, the average of the three maximum tolerated doses by the three patients will be defined as MSD for part 2. With this design, we aim to find the highest dose that generates, if any at all, at maximum only transient mild/moderate AEs. At the same time, this will allow to glean information on clinical effect for the planning of a potential phase II study.

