#### 6.1.2 Dose consolidation (Part 2)

The MSD will then be administered repeatedly (8 times over 8 weeks) to 9 additional patients to consolidate what will be found in the escalation part.

At the first infusion, blood will be recovered for PK analysis over 96 h (see **Section 9.2.2 Assessment of Secondary Outcomes**). The expected half-life is projected to be 30 h (extrapolation from pre-clinical studies). Therefore, 96 h would suffice to obtain 3 half-life periods and to observe enough tapering.

Throughout this part 2, all patients will be monitored weekly to record AE and document them. The clinical and PD assessment will be performed similarly to the dose escalation. This part will provide more information on the tolerability of the chosen MSD over repeated injections. This will complete the safety profile while avoiding to mobilize the whole cohort of patients for the dose escalation. This is still a modest number of patients but this will suffice to evidence the most common AEs associated with the treatment. Moreover, potential clinical effects on signs and symptoms of PD can be studied in view of the planning of a phase II study.

In this multiple dose administration part, patients that drop out for reasons unrelated to the treatment with TLN will be replaced due to the small number of patients involved.

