#### 6.1.3 Continued TLN infusions

Patients wishing to continue their treatment beyond the assessments in part 1 of the trial described above, can receive further weekly TLN infusions for up to 8 additional weeks at their personal MSD or at the dose level 14. A lighter schedule (one instead of two visits per week) than part 1 was elected for the patients' convenience. All patients will be monitored weekly to record AE and assessed based on details given in chapter **9. ASSESSMENTS**.

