#### Part 1 – Dose Escalation:

The drug will be administrated in a single ascending dose (SAD) as a once weekly i.v. infusion in 3 patients up to 14 dose levels or until unacceptable toxicity appears (see section **6.1.1 Dose escalation** for details on the sequence between patient 1 and 2/3).

The aim of this dose escalating procedure is to define the MSD in terms of the occurrence of AEs dependent on their seriousness, intensity and causality according to the standards and definitions given in this trial protocol (see section **8.3 Doses modifications**).

|               |        |
|---------------|--------|
| Dose level 1  | 6 mg   |
| Dose level 2  | 12 mg  |
| Dose level 3  | 60 mg  |
| Dose level 4  | 120 mg |
| Dose level 5  | 180 mg |
| Dose level 6  | 240 mg |
| Dose level 7  | 300 mg |
| Dose level 8  | 360 mg |
| Dose level 9  | 420 mg |
| Dose level 10 | 480 mg |
| Dose level 11 | 540 mg |
| Dose level 12 | 600 mg |
| Dose level 13 | 660 mg |
| Dose level 14 | 720 mg |

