#### Part 2 – Dose consolidation:

As soon as the MSD is defined, 9 patients will receive the full MSD in the multiple dose administration part once a week for 8 weeks.

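### The DSMB meeting set for dose level 15 cannot occur on a 14-level ladder, and nothing shown places the DSMB's review of the upper doses before Part 2 starts

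*Protocol*

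**What the plan says.** **DSMB meetings.** Under section 1.7 the board is to "meet after dose level 5, 10 and 15 during part 1 of the trial, after the maximal suitable dose (MSD) has been defined", with a last meeting after last patient last visit. The same section calls the board advisory and adds: "More details are provided in the trial specific DSMB charter".

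**Ladder.** Section 8.1.1 gives Part 1 as a "once weekly i.v. infusion in 3 patients up to 14 dose levels" and lists each level, the last being level 14 at 720 mg. Section 6.1.1 stops at the same dose, section 4.2 speaks of at most 14 escalating doses, and section 6.1.3 lets Part 1 patients continue "at their personal MSD or at the dose level 14".

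**Order of dosing in Part 1.** Section 6.1.1 staggers the patients: "every week patient 1 will receive one dose at the same time that patients 2 & 3 receive the preceding dose". The Part 1 schedule narrative, which follows section 8.9 and introduces the section 9 tables, instead has the three patients ideally starting together, each at 6 mg.

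**Move to Part 2.** At the end of escalation, "the average of the three maximum tolerated doses by the three patients will be defined as MSD for part 2" (section 6.1.1). Section 6.1.2 continues: "The MSD will then be administered repeatedly (8 times over 8 weeks) to 9 additional patients". Section 8.1.1 states: "As soon as the MSD is defined, 9 patients will receive the full MSD in the multiple dose administration part".

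**Other oversight.** Under section 1.6 the Internal Monitoring Committee (IMC) is the executive body. It meets weekly during treatment, includes an external physician, and must be unanimous for each patient to continue.

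**The concern.** One of the three level-tied DSMB reviews in Part 1 depends on a dose level that does not exist. Followed literally, that meeting is never called.

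The upper part of the ladder then depends on the meeting held after the MSD is defined. Definition of the MSD is also the event that starts Part 2, and the protocol does not say which comes first. A site that gave the first Part 2 infusion before the DSMB met would still comply with the protocol text.

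The transition is a real step in exposure. Part 1 patients climb from 6 mg, whereas Part 2 patients are new to the drug, receive the full MSD at their first infusion, and then receive it weekly for 8 weeks. The MSD comes from three patients. Section 3.4 reports no earlier clinical data on the product, and section 6.1.1 concedes that Part 1 does not assess cumulative effects at a constant dose. An independent look at the raw data is most useful at this point.

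**Working it through.** **Inputs.** Ladder: sections 6.1.1 and 8.1.1. DSMB triggers: section 1.7. Stagger: section 6.1.1. Concurrent start: the Part 1 schedule narrative. MSD rule: sections 6.1.1 and 9.2.2.

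**Step 1: count the levels.** Doses are 6 and 12 mg, then 60 to 720 mg in 60 mg steps. The steps number 720/60 = 12, so the total is 2 + 12 = 14, matching the protocol. A 15th level on the same rule would be 720 + 60 = 780 mg, which is planned nowhere.

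**Step 2: what has been given by the level-10 meeting.** Under the stagger and without delays, patient 1 receives level k in week k, and patients 2 and 3 receive it in week k + 1. Under a concurrent start, all three receive level k in week k.

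| Reading of the level-10 meeting | Week | Patient 1 highest | Patients 2 and 3 highest | Levels not yet given |
|---|---|---|---|---|
| Stagger, all three have had level 10 | 11 | level 11, 540 mg | level 10, 480 mg | 12–14 (600–720 mg) |
| Stagger, patient 1 has had level 10 | 10 | level 10, 480 mg | level 9, 420 mg | 11–14 (540–720 mg) |
| Concurrent start | 10 | level 10, 480 mg | level 10, 480 mg | 11–14 (540–720 mg) |

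On every reading, levels 12 to 14 have no level-tied meeting after them. Level 11 has at most one exposed patient by the level-10 meeting. The top dose is 720/480 = 1.5 times level 10.

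**Step 3: does the size of the MSD decide whether there is a gap?** No. The MSD is the mean of three individual maxima. Maxima of 720, 360 and 360 mg give (720 + 360 + 360)/3 = 480 mg, yet one patient went through levels 12 to 14 after the level-10 meeting. The gap exists when any patient goes above level 10, whatever the mean.

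**Step 4: compare the two events.** The DSMB meets after the MSD is defined (1.7). Part 2 dosing follows as soon as the MSD is defined (8.1.1; 6.1.2 says only that it comes next). Both follow the same event, and neither is placed before the other. The first Part 2 treatment visit (section 9.3.9) lists no DSMB condition.

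**The case against.** **The missing meeting removes little review.** The MSD is defined at the end of escalation. If escalation runs to the top, an end-of-ladder meeting and the MSD meeting fall at the same point and see the same data. This stands. A reader might infer that the DSMB never reviews levels 12 to 14 before the trial ends. The documents do not support that, because section 1.7 schedules the MSD meeting.

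**The interval is not unusually long.** Under the stagger, level 10 is complete in all three patients in week 11 and level 14 in week 15, which is 15 − 11 = 4 weeks. Four levels is less than the five-level spacing used earlier in section 1.7. This also stands, so the interval itself is not the harm.

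**The order may be settled elsewhere.** A meeting tied to the MSD and listed apart from last patient last visit reads naturally as a review before Part 2, and the charter may say so. A reader might go further and infer that the protocol contradicts itself or sends Part 2 ahead without the DSMB. It does neither. The order is simply unstated, and the charter and the section 6.1 figure are not available to check.

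**A DSMB hold would be a new power.** The board is advisory and the IMC decides. This stands and shapes the remedy: the meeting should come first, but the decision should stay with the IMC.

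**The number 15 may mean week 15**, the last infusion week under the stagger. That is possible, but the text says dose level, so it would need correcting on that reading too.

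**Conclusion.** The level-15 trigger is wrong as written and cannot fire. This holds on every reading of the ladder.

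The consequence is narrower than a lost safety review. Before last patient last visit, DSMB review of levels 12 to 14 (or 11 to 14, depending on the start pattern and on whose level 10 triggers the meeting) rests on one meeting. Its order relative to the first Part 2 infusion is not fixed in the text shown. The exposure gap arises only if at least one patient goes above level 10, which is the planned course if tolerability allows.

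The week counts assume no dose delays. The ordering point assumes that the charter does not already set the sequence. Weekly IMC review with an external physician, who can block a step, limits the risk to patients. Severity is minor to moderate.

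**What to change.** - **Section 1.7:** replace the level-15 trigger with dose level 14 or the end of Part 1, whichever comes first, and combine this with the MSD meeting. The alternative trigger is needed because escalation can stop before level 14.
- **Sections 6.1.2 and 8.1.1 (Part 2):** state that the first Part 2 infusion is given only after that DSMB meeting has taken place and the IMC has considered its advice. The board stays advisory.
- **DSMB charter:** align it if it does not already say this.

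No dose, stopping rule or sample size changes, and no extra meeting is needed. The cost is a wording amendment and a pause estimated at days to about a week before Part 2. The pause can overlap Part 2 screening, which may run up to 28 days before each patient's start.
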